#### Study population

Patients with incident primary breast cancer are eligible for recruitment into the B2B Cohort if they meet the following criteria as determined through the CoBRA database: (1) histologically-confirmed stage I to stage IIIc breast cancer diagnosed between 2010 and 2015; (2) residents of Calgary, Alberta and the surrounding areas; (3) females ≥18 and ≤80 years at initial diagnosis; (4) able to provide informed, written consent and complete questionnaires and an in-person interview in English; and, (5) no previous cancer diagnosis with the exception of cervical in-situ neoplasia (CIN) and non-melanoma skin cancer. Cohort participants must have donated a pre-surgical blood sample to the ACRB (Fig. 3) and indicated willingness to be contacted for future research. The contact details of eligible patients are then exported to the B2B Research Program database for recruitment into the B2B Cohort. The B2B Cohort is restricted to the Calgary area because of the feasibility of processing blood samples collected from community laboratories within 24 h.

**Fig. 3 Fig3:**
[figure not shown]
Ascertainment recruitment, data and biospecimen collection and sharing scheme. Newly diagnosed cancer patients are identified through the ACR, and are invited to donate biospecimen samples by the ACRB utilizing the CoBRA infrastructure. Clinical data and biospecimens are stored by the ACRB, and contact information from eligible and consenting participants is sent to study coordinators of relevant research programs. Subsequent blood samples and blood questionnaire data for routine study follow-up are collected by the ACRB and act as a shared resource between the biorepository and research study team

#### Recruitment

The recruitment of patients into the B2B Cohort was harmonized with recruitment for the **A**lberta **M**oving beyond **B**reast canc**ER** (AMBER) study [92] because the potential participants are drawn from the same population of breast cancer patients (Fig. 4). If a patient agrees to be contacted regarding future research, contact details for all eligible patients are imported into the *AMBER & B2B Recruitment Database*. Patients are first invited to participate in the AMBER study so that their exercise assessments can be completed prior to the delivery of systemic therapy [92].

**Fig. 4 Fig4:**
[figure not shown]
B2B/AMBER participant recruitment. Eligible patients are identified by the ACRB through CoBRA processes, and the contact details of consenting biospecimen donors are sent to a recruitment database shared by both the AMBER and B2B study coordinators. Patients are invited to participate by each study, and if they agree, their information is then imported into the specific study database. Some information sharing occurs between the AMBER and B2B study database, such as whether or not shared questionnaires have been completed

Patients are invited to participate in the B2B Cohort approximately 6–8 weeks post-surgery, and after potential recruitment into the AMBER study. The B2B Research Program Study Coordinator contacts eligible women by telephone to explain the research program. If the potential participant verbally agrees to receive the recruitment package, their information is imported into the *B2B Tracking Database* and they are mailed a letter of invitation, consent information brochure, consent form and *Pre Interview Worksheets*.

Consenting participants complete baseline worksheets, an in-person interview and post-interview questionnaires within six months of an initial breast cancer diagnosis, with follow-up assessment occurring at 24, 48 and 72-month intervals post-diagnosis. Passive follow-up, through chart abstraction of medical records, will occur at 10 years following the completion of the active follow-up or for those who were lost to follow-up but did not withdraw consent. We anticipate that the recruitment of the baseline B2B Cohort will be completed by August 2015; recruitment of the baseline cohort of >600 participants will have taken a total of 5.5 years. Analysis of data and biospecimens will commence shortly afterwards.

#### Sample size

As a core infrastructure resource, the B2B Cohort sample size was not explicitly based on the power to address a single hypothesis. However, to address our primary, outcome–based hypotheses embedded within the core projects, we will follow all cohort members (~600 patients) for a median of five years. Less than 60 % of breast cancer recurrences are apparent within three years of follow-up but ~80 % are evident after five years of follow-up [3, 9, 10]. Within the 10-year time frame of the B2B Research Program, we expect 70-80 women to present with clinically evident bone metastases [3, 9, 10]. Using serum vitamin D concentrations as an example a specific hypothesis to be tested, broad inter-quintile ranges of serum [25-OHD] that are typical within North American populations (Q1 < 14.9 ng/ml, Q5 > 35.3 ng/ml [93]). Therefore, we anticipate that, for the vitamin D and inflammation analyses, a 20 % difference in vitamin D exposures and inflammatory status between women with and without bone metastases will provide 80 % power to detect a relative risk for bone metastases of 1.8 even with this modest sample size. We anticipate that similar effect magnitudes will be observed in the other core projects.

#### Data collection instruments

##### Pre-interview worksheets

Each participant is mailed pre-interview questionnaires including the *Sun Exposure Worksheets* and *Past Year Dietary Worksheets* as part of their recruitment package. Participants are asked to complete these questionnaires and return them by mail. The *Sun Exposure Worksheets* collect information on residence, work history and vacation history for three time periods: the 12 months prior to breast cancer diagnosis; the calendar year five years prior to breast cancer diagnosis; and the calendar year 10 years prior to breast cancer diagnosis. Although eligible participants must be free of detectable distant metastases at diagnosis, breast cancer cells can be disseminated early in tumour development. Capturing exposure data for an extended pre-diagnostic period, and during follow-up, ensures that exposure can be estimated for the entire period that a patient was at risk of disease dissemination.

The *Past Year Dietary Worksheets* collect data regarding food intake and frequency in the 12 months prior to breast cancer diagnosis, and was developed to assess intake of certain foods and supplements that have high vitamin D and calcium content, consumed at a reasonable frequency by female study participants in Alberta [94]. The sun exposure, dietary, and supplement data will be used to estimate levels of vitamin D during the relevant exposure period.

##### In-person interview

The completed pre-interview questionnaires are scanned using TELEform®, an optical character recognition software program, then verified by study staff for completeness before being exported into the Blaise® computer-assisted interviewing draw 1software program to pre-populate corresponding responses in the *B2B Baseline Interview*. Furthermore, if the participant has completed the AMBER *Baseline Health Questionnaire* (BHQ), those verified responses are also used to pre-populate corresponding responses in the *B2B Baseline Interview*. By pre-populating the interview with information provided by the participants in the pre-interview questionnaires and the AMBER BHQ, we reduce participant interview burden and expedite the in-person interview process.

One of the B2B Interviewers conducts the in-person interview at a time and place convenient for the participant. The *B2B Baseline Interview* is typically an hour in length, and collects information regarding pregnancy and menstruation, menopausal status, hormone replacement therapy, birth control and hormone contraceptive use, personal health history/co-morbidity, medications (over-the-counter and prescription), vitamins, minerals and herbal supplements, mobility and physical activity, sun exposure, diet history, family history of cancer, smoking habits, alcohol consumption history, and demographic information. Following the in-person interview, the participant is provided with a Canadian *Diet History Questionnaire* II (*DHQ II*) and *Past Year Total Physical Activity Questionnaire* (*PAQ*) [95], which is to be completed and returned to the study office by mail. If a B2B participant has already completed the *DHQII* and *PAQ* as part of the AMBER study, these responses are made available to the B2B Research Program to further reduce participant burden.

##### Physical activity questionnaire

The *PAQ* is administered at four time points throughout the study: baseline (post-interview), 24, 48 and 72-month follow-up. The *PAQ* is a self-administered questionnaire in which participants report their occupational, transportation, household and recreational/leisure physical activities over the previous 12 months. Participants report the number of hours spent in each activity per week, allowing for analysis of each individual type of activity as well as a summation of all four categories of activities to determine the participant’s total amount of physical activity over the past year [95]. These measures are expressed as metabolic equivalents for each activity and are reported in total MET-hours/week/year of activity [95].

##### Diet history questionnaire

The *DHQ II* [96] is also administered at four time-points during the study at baseline (post-interview), 24, 48 and 72-month follow-up. It is a self-administered food frequency questionnaire developed initially by the National Institute of Health and then adapted for use in the Canadian population [96]. This FFQ is a comprehensive assessment of dietary intake in the previous 12 months that has 164 questions about 134 food items and includes seasonal intake of a variety of foods, the portion size and frequency of intake for each food item. Responses from the *DHQII* provide comprehensive information on dietary habits, output of nutrients and the amount foods and food groups consumed. Additionally, the dose and frequency of vitamin and mineral supplementation over the past year is also obtained.

##### Biospecimen collection

Each participant’s baseline blood sample is collected as part of their ascertainment and upstream recruitment into the ACRB according to the CoBRA procedures. Participants receive a blood requisition form and are asked to donate a blood sample at any Calgary Laboratory Services location. The baseline collection consists of a 60 ml of blood sample collected in six 6 ml Red Top (clot activator) vacutainers and four 6 ml Lavender Top (EDTA) vacutainers. The vacutainers are transported to a central processing laboratory and fractionated by centrifugation to yield a total of 48 aliquots comprised of 26 serum, 14 plasma, 4 buffy coat and 4 red blood cells (400–500 μl per aliquot) in 1 ml Matrix® 2D-barcoded tubes (Thermo Fisher Scientific Inc.). At the time of blood collection, participants also complete a short *Blood Questionnaire* that records information regarding their fasting status, recent smoking, medication, supplement use, family history of cancer and menstrual status.

Hematoxylin and eosin stained slides corresponding to formalin-fixed paraffin embedded (FFPE) tissue blocks are retrieved for all participants for whom tissue is available. Archived tissue blocks will be requested and retrieved according to the H&E slide pathology review; the pathologist will mark the area of the block from which triplicate 0.6 mm tissue cores should be collected for the construction of TMAs. In addition to the collection of tissue cores, 10 μm tissue scrolls will be collected for the extraction of nucleic acids (DNA and RNA). The RNA will be used for the transcript analysis in sub-project 2 and the DNA will be extracted at a later date for ancillary projects potentially investigating mutational analyses. All blood and tissue samples are stored within the ACRB.

##### Participant follow-up at 24, 48 or 72-months

Additional data and biospecimen collections occur at the specified follow-up intervals of 24, 48 and 72-months from the participant’s primary breast cancer diagnosis. Each month, the Study Coordinator queries the *B2B Recruitment Database* to generate a list of participants eligible for follow-up. The Study Coordinator contacts each participant by telephone to confirm their address and willingness to continue their participation in the B2B Research Program. If they agree, participants are sent a follow-up package that includes a *PAQ*, *DHQ II* and the appropriate *Follow-Up Questionnaire* (24, 48 or 72-month); these are self-administered questionnaires to be completed by the participants and returned by mail to the study office. The *24, 48 or 72-month Follow-Up Questionnaires* request information on: personal health history, breast cancer progression (only at 24 month follow up only), recurrence, contra-laterality and new primary diagnosis, medications (prescription and over the counter), smoking habits, alcohol consumption, sun exposure, dietary intake, mobility and physical activity and anthropometric measurements.

Follow-up blood samples are also collected at 24, 48 and 72 months. Each Follow-Up Package contains a *Research Blood Requisition* form and participants are asked to donate a blood sample at any Calgary Lab Services location. The follow-up blood collections consist of a 30 ml of blood sample collected using three 6 ml Red Top (clot activator) vacutainers and two EDTA vacutainers. Again, the vacutainers are transported to a central processing laboratory, fractionated by centrifugation to yield serum, plasma red blood cells and buffy coat and stored in 32 aliquots of 400–500 μl in 1 ml Matrix® 2D-barcoded tubes (Table 1).

##### Vital status check

The vital status of each participant is checked before each follow-up contact at 24, 48 and 72 months through a record linkage done by the Department of Cancer Surveillance (Alberta Health Services). Vital Statistics Alberta (VSA) provides information on all deaths that occurred in the province to the ACR, on request, with underlying cause of death provided by Statistics Canada to VSA. There is an average three-month time lag between the actual death occurrence and reporting to the ACR. Several mechanisms, such as reciprocal agreements between other provinces and record linkages with the Canadian Mortality Database, exist to capture the deaths of participants who left the province of Alberta after their diagnosis. These agreements and processes ensure that vital status can be determined for over 95 % of participants. Cause and date of death will also be obtained from this source.

##### Medical record abstraction

Medical record abstraction will occur in the final year of the B2B Program operation (commencing August 2018). Health Record Technicians from the ACR will use direct data entry to a medical record abstraction form to collect data from the medical records (both paper and electronic charts) for all participants in the B2B Cohort. The medical record abstraction form was developed from standardized forms used in our past physical activity and breast cancer cohort study conducted in Alberta [97, 98].

Baseline pathologic data, including clinical stage and pathologic stage (according to American Joint Committee on Cancer criteria [99], tumor size, grade, histology, estrogen receptor status, progesterone receptor status human epidermal growth factor receptor 2 status, type and results of computerized tomography or positron emission tomography scans, status of margins (with breast conserving surgery), and pathology of lymph nodes (if surgically sampled) are provided by the ACRB/CoBRA database and verified during the medical record abstraction. Abstracted variables will include the type of surgery, and all treatment and follow-up care including data on chemotherapy, radiation therapy, and hormone therapy. Treatment completion rates will be estimated for chemotherapy and hormone therapy but not for radiation therapy since few patients fail to complete radiation therapy. For chemotherapy completion rate, we will estimate the average relative dose intensity (RDI) received for the originally planned regimen based on standard formulae as we have done in a previous RCT [100]. For hormone therapy, the follow-up questionnaires ask participants to report if they have stopped taking their prescribed hormone therapy at any time before its intended completion and the reasons for stopping.

Disease endpoints are defined according to the Standardized Definitions for Efficacy End Points in Adjuvant Breast Cancer Trials [101]. Our primary endpoint of interest is bone metastasis or a skeletal-related event according to the definition in the NSABP 34 trial (http://clinicaltrials.gov/show/NCT00009945). We will also examine other composite disease endpoints as secondary endpoints including overall survival, distant disease-free survival, distant relapse-free survival, and distant recurrence-free interval. Finally, we will examine the single disease endpoints of death from breast cancer and death from non-breast cancer. For participants who have left the province and who are not known to be deceased, the date of leaving Alberta will be used as the censoring time.

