**Methods/Design:**

The B2B Research Program is enrolling a prospective cohort of 600 newly diagnosed, incident, stage I-IIIc breast cancer survivors in Alberta, Canada over a five year period. At baseline, pre-treatment/surgery blood samples are collected and detailed epidemiologic data is collected by in-person interview and self-administered questionnaires. Additional self-administered questionnaires and blood samples are completed at specified follow-up intervals (24, 48 and 72 months). Vital status is obtained prior to each follow-up through record linkages with the Alberta Cancer Registry. Recurrences are identified through medical chart abstractions. Each of the four projects applies specific methods and analyses to assess the impact of serum vitamin D and cytokine concentrations, tumour transcript and protein expression, serum metabolomic profiles and *in vitro* cell signalling on breast cancer bone metastases.

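### Women who leave Alberta are censored at departure only if no death is later recorded, so death rates are biased upward by about 1–8% over six years at assumed departure rates of 0.5–3% a year

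*Protocol article*

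**What the plan says.** The endpoint paragraph closing the Medical record abstraction section of the protocol article names bone metastasis or a skeletal-related event as primary. It then lists "secondary endpoints including overall survival, distant disease-free survival, distant relapse-free survival, and distant recurrence-free interval", and adds that "we will examine the single disease endpoints of death from breast cancer and death from non-breast cancer". One sentence on the censoring time follows, with no exception for any endpoint: "For participants who have left the province and who are not known to be deceased, the date of leaving Alberta will be used".

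The Vital status check section describes interprovincial agreements and linkage to the national mortality database, which "exist to capture the deaths of participants who left the province of Alberta after their diagnosis". It continues: "These agreements and processes ensure that vital status can be determined for over 95 % of participants", and "Cause and date of death will also be obtained from this source".

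Disease status comes from elsewhere. The abstract says: "Recurrences are identified through medical chart abstractions". The Medical record abstraction section assigns this work to technicians of the Alberta registry. The follow-up section adds mailed questionnaires at 24, 48 and 72 months that ask about recurrence.

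**The concern.** A censoring rule may use only what is known at the time of censoring. This one looks ahead. Of two women who leave in the same month, the one who later dies is kept to her death and counted as an event; the one who survives is removed at departure. Events after departure enter the numerator, but the matching event-free time is missing from the denominator. The direction is therefore known: estimated mortality is too high. The error does not shrink with sample size.

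The handling of leavers known to be dead is implied rather than written out. But if all leavers were meant to be censored at departure, the condition about death would have no function.

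At stake are the absolute rates of overall and cause-specific death, and of the distant-disease composites in so far as they count death. Relative comparisons are at risk too if an exposure is related to leaving the province.

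**Working it through.** The article states no figure that depends on this rule, so there is nothing to reproduce. The check is of direction and size.

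**From the article:** the rule; capture of deaths after departure; vital status known for over 95%; about 600 women (Sample size); six years of active follow-up (Lessons and limitations); passive chart follow-up ten years after active follow-up ends (Recruitment).

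**Assumed, because the article gives no figure:** departure rate μ of 0.5–3% per year; five-year mortality p of 10–20%, so the death rate λ = −ln(1 − p)/5 is 0.021 to 0.045 per year; departure independent of death; a share c = 0.95 of deaths after departure captured, taken from the overall 95%.

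**Formula with full capture**, follow-up T, per woman:
- events = 1 − e^(−λT)
- true person-time P = (1 − e^(−λT))/λ
- person-time dropped from women alive at T: X = e^(−λT) × [T − (1 − e^(−μT))/μ]
- estimated/true death rate = P/(P − X)

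**One case**, λ = 0.03, μ = 0.02, T = 6:
- P = (1 − 0.8353)/0.03 = 5.491 years
- X = 0.8353 × (6 − 5.654) = 0.289 years
- ratio = 5.491/5.202 = 1.056
- deaths after departure per 600 women: 600 × [0.1647 − (0.03/0.05)(1 − e^(−0.30))] = 600 × 0.0092, about 5.5

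**With capture c**, events are (deaths before departure) + c × (deaths after departure), and person-time is c(P − X) + (1 − c)(1 − e^(−(λ+μ)T))/(λ + μ). For c = 0.95, T = 6 and five-year mortality of 10–20%:

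| Departures per year | Share leaving within 6 years | Estimated/true death rate |
|---|---|---|
| 0.5% | 2.6–2.8% | 1.012–1.013 |
| 1% | 5.1–5.5% | 1.025–1.027 |
| 2% | 9.9–10.6% | 1.050–1.054 |
| 3% | 14.5–15.5% | 1.076–1.082 |

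Simulation with 4 million women per setting agrees to within simulation error.

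**Longer follow-up** (15% five-year mortality, 2% departures): 1.05 at 6 years, 1.08 at 10 and 1.12 at 16, which is six active plus ten passive years.

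**Alternative rules, same settings:** censoring every leaver at departure gives 1.00; following every leaver by linkage gives 0.99–1.00.

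**Dependence on capture** (15% mortality, 2% departures, 6 years):

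| Deaths after departure captured | Rule as written | Follow all by linkage |
|---|---|---|
| none | 1.00 | 0.94 |
| half | 1.03 | 0.97 |
| 95% | 1.05 | 1.00 |

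**Relative comparisons.** If leaving is equal across exposure groups, the inflation nearly cancels. If one group leaves at 3% and the other at 0.5% per year, a null exposure shows a rate ratio of 1.076/1.012 to 1.082/1.013, about 1.06–1.07.

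**Bone metastasis.** If leavers known to be dead were kept at risk until death, the time between departure and death would be about 2–22 person-years per 600 women over six years, or 0.06–0.7% of person-time.

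**The case against.** The strongest reply is that the size is modest and the endpoints hit are not the primary one. At 0.5–1% departures per year the bias is 1–3%. With an assumed 60–120 deaths, the 95% interval on the rate is about ±1.96/√120 to ±1.96/√60, or ±18% to ±25%. The Sample size section frames its example hypothesis as a relative risk, where equal departure cancels most of the error. All of this stands and lowers the severity. It does not remove the error, which is systematic and avoidable.

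A second reply is that endpoint-specific censoring is commonly left to an analysis plan that is not shown. That protects what the article leaves unsaid. It does not protect a sentence that fixes a rule.

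Three stronger readings are tempting and are not supported:
- *The primary endpoint is compromised.* A reader might infer that leavers who die remain at risk for bone metastasis with no means of detecting it. The article does not say how they are handled for that endpoint. Access to charts outside the province is not stated either way, and a woman who has moved can still return a mailed questionnaire. Even on the worst reading, at most about 0.7% of person-time is affected.
- *The bias is 11–12%, or creates a rate ratio of about 1.11.* These sizes need about 19% of women to leave, or 26% against 10% by exposure. Nothing in the article supports departure on that scale.
- *Censoring every leaver at departure is free of bias.* The ratio of 1.00 arises because departure was assumed unrelated to death. If ill women move to be near family, that rule would bias mortality downward.

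**Conclusion.** The concern holds for the death endpoints. Read with the Vital status check section, the stated rule makes censoring depend on a later death and biases upward the rates of overall, breast-cancer and non-breast-cancer death, and the death component of the composites. The inflation is about 1–8% over six years and grows with longer follow-up. The direction follows from the text, provided that some deaths after departure are captured, as the article says. The size rests on assumed departure rates of 0.5–3% per year, 95% capture and departure independent of death; it hardly changes across five-year mortality of 10–20%. Relative comparisons are affected mainly where leaving differs by exposure. For bone metastasis and recurrence the effect is small and conditional on whether disease status outside the province can be observed. This should be fixed; because the endpoints mainly affected are secondary, it is not critical to the program's main aim.

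**What to change.** Replace the sentence with a rule that does not refer to later vital status, and apply it to all leavers alike.

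- **Overall and cause-specific death:** preferably follow every leaver through the linkage already described, and count those without a death record as alive to the linkage date. Confirm first that capture is good among leavers themselves. If 10% leave, over 95% completeness overall could still leave nearly half of leavers unresolved (5%/10%), and at half capture this option would understate the rate by about 3%. The alternative is to censor every leaver at departure, stating the assumption that departure is unrelated to prognosis.
- **Bone metastasis and recurrence endpoints:** censor every leaver at departure, or at the last date on which her disease status could be observed, whether or not she later dies.
- **Composites that count death:** choose one of these rules and state it, so that death and recurrence are followed over the same period.

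The cost is a few sentences of wording and no new data source. A few deaths after departure may drop out of some analyses: in the worked case, at most about 5 or 6 per 600 women.
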